### 10.3 Selection of dose in the study

In the phase III PROUD-PV study (EUDRA-CT 2012-005259-18), AOP2014 is used at the starting dose of 100µg biweekly. This is equivalent to a pegIFN 2a dose of approximately 70 µg weekly. Previous clinical studies suggested that a dose of 45-90µg pegIFN weekly is therapeutically effective. At the lower dose of 45µg pegIFN weekly was associated with a well manageable toxicity. **Therefore, a dose of 100µg AOP2014 to be administered biweekly was chosen as the standard dose for the ENDURE-CML study.**

To achieve a good tolerability of AOP2014 the study treatment will be escalated to full maintenance dose of 100µg as follows: 50 µg AOP2014 every 14 days for the first 4 weeks. From week 5 patients will receive full dose of 100µg once per two weeks.

#### 10.3.1.1 Dose reductions and modifications

Dose modifications will be performed in the case of hematological or non-hematological side effects. A complete list of AOP2014 side effects can be found in the current "Investigator's Brochure" (see 10.6). There is limited experience with AOP2014 overdosage. The study, conducted in Austria (AOP Pegivera study) is an ongoing phase I/II study with the primary objective to identify the maximum tolerated dose (MTD) of AOP2014 in patients, diagnosed with polycythemia vera. Safety and tolerability is being assessed and an exploratory analysis of efficacy and biomarker modulation will be performed in this study. 51 patients were included into the study (recruitment closed). No DLTs were observed at the dose levels up to 540 µg every two weeks, and sound efficacy observations could be done. There is no specific antidote for pegIFN. Hemodialysis and peritoneal dialysis are not effective.

##### 10.3.1.1.1 Dose modification in case of hematological toxicity

Table 3 displays the recommended AOP2014 dosage modifications due to neutropenia, or thrombocytopenia. Following improvement of the adverse reaction, neutropenia or thrombocytopenia, consider re-escalation of the dosage back to the previous dosage.

| Laboratory Values                           | Recommended pegIFN Dosage                                                                                                                                                                                                                            |
|---------------------------------------------|------------------------------------------------------------------------------------------------------------------------------------------------------------------------------------------------------------------------------------------------------|
| Neutropenia                          |                                                                                                                                                                                                                                                      |
| ANC < 750 cells/mm              | Reduce to 50 µg once every 14 days
Increase to standard dose once ANC count returns to >750 cells/mm                                                                                                                                  |
| ANC < 500 cells/mm              | Hold treatment until ANC values return to 1000 cells/mm  or more. Reinstitution at 50 µg once every 14 days and monitor ANC.
Increase to standard dose once ANC count returns to >750 cells/mm                            |
| Thrombocytopenia                     |                                                                                                                                                                                                                                                      |
| Platelet < 50,000 particles/mm  | Reduce to 50 µg once every 14 days                                                                                                                                                                                                                   |
| Platelet < 25,000 particles/mm  | Discontinue treatment until platelets return to 75.000 particles/mm  or more. Reinstitution at 50 µg once every 14 days and monitor platelets.
Increase to standard dose once platelet count returns to >75.000 cells/mm  |

**Table 3 Recommended AOP2014 dosage modifications for neutropenia and thrombocytopenia**

**10.3.1.1.2 Dose modifications in case of non-hematological toxicity: depression**

| Depression Severity | Initial Depression Management (4-8 weeks)           |                                                                | Depression Management After 8 Weeks                        |                                                                                                                                          |                                                                                                |
|---------------------|-----------------------------------------------------|----------------------------------------------------------------|------------------------------------------------------------|------------------------------------------------------------------------------------------------------------------------------------------|------------------------------------------------------------------------------------------------|
|                     | Dosage Modification                                 | Visit Schedule                                                 | Depression Severity Remains Stable                         | Depression Severity Improves                                                                                                             | Depression Severity Worsens                                                                    |
| Mild                | No change                                           | Evaluate once weekly by visit and/or phone                     | Continue weekly visit schedule                             | Resume normal visit schedule                                                                                                             | Consider psychiatric consultation. Discontinue AOP2014 or reduce dosage to 50 µg every 14 days |
| Moderate            | Decrease AOP2014 dosage to 50 µg once every 14 days | Evaluate once weekly (office visit at least every other week). | Consider psychiatric consultation. Continue reduced dosing | If symptoms improve and are stable for 4 weeks, you may resume normal visit schedule. Continue reduced dosage or return to normal dosage | Obtain immediate psychiatric consultation. Discontinue AOP2014 permanently.                    |
| Severe              | Discontinue AOP2014 permanently                     | Obtain immediate psychiatric consultation.                     | Psychiatric therapy necessary.                             |                                                                                                                                          |                                                                                                |

**Table 4** Recommended dosage modification for depression management**10.3.1.1.3 Dose modifications in case of non-hematological toxicity: Liver toxicity**

Following improvement of liver toxicity, re-escalation of the dosage back to the previous dosage should be warranted.

| Laboratory Abnormality            | Severity                                                               | Recommended AOP2014 dosing modification |
|-----------------------------------|------------------------------------------------------------------------|-----------------------------------------|
| Increased transaminase (ALT, AST) | For persistent or increasing elevations $\geq 5$ but $< 10 \times$ ULN | Modify dosage to 50 µg every 2 weeks    |
|                                   | For persistent ALT values $\geq 10 \times$ ULN                         | Discontinue treatment                   |

**Table 5** Recommended Dose modification in case of liver toxicity**10.3.1.1.4 Dose modifications in case of other non-hematological toxicity**

| Severity       | Recommended AOP2014 Dosage Modification           |
|----------------|---------------------------------------------------|
| WHO I - II CTC | No dosage modification                            |
| WHO II CTC     | Modify dosage to 50 µg every 2 weeks              |
| WHO III CTC    | Pause treatment until recovery to WHO I or II CTC |
| WHO IV CTC     | Discontinue treatment                             |

**Table 6** Recommended Dose modifications in case of other non-hematological toxicities

For WHO CTC version and list please refer to the NCI CTC4.03.

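### Table 6 gives two incompatible dose instructions for grade II non-hematological toxicity; in Table 3 the re-escalation thresholds are already met by the counts that permit restart

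*Protocol*

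**What the plan says.** **Table 6, section 10.3.1.1.4.** The table has four rows by toxicity grade. The first is "WHO I - II CTC | No dosage modification". The second is "WHO II CTC | Modify dosage to 50" µg every two weeks. The third, for grade III, is "Pause treatment until recovery to WHO I or II CTC"; it names no restart dose. The fourth, for grade IV, stops treatment. The only note under the table points to the CTC version.

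**Table 3, section 10.3.1.1.1.**
- ANC below 500: "Hold treatment until ANC values return to 1000 cells/mm"³ or more, restart at 50 µg every 14 days with ANC monitoring, then "Increase to standard dose once ANC count returns to >750 cells/mm"³.
- Platelets below 25,000: stop until platelets reach 75,000 or more, restart at 50 µg with platelet monitoring, then "Increase to standard dose once platelet count returns to" above 75,000.
- Platelets below 50,000: reduce to 50 µg. The row gives no value for going back up.

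A sentence above Table 3 invites the investigator to consider returning to the previous dose once neutropenia or thrombocytopenia has improved. It gives no threshold.

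**Dose schedule (Synopsis; section 10.3).** Arm A receives 50 µg every two weeks for the first four weeks and 100 µg every two weeks from then on.

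**The concern.** A dose table should give one answer for each grade. Table 6 gives two for grade II, and they exclude each other: leave the dose alone, or change it to 50 µg. The grade III row adds to this, because a patient whose treatment was paused may resume on recovery to grade II, which is the grade with two answers.

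The events concerned are foreseeable. Section 10.2 lists influenza-like illness, fatigue, arthralgia and myalgia as very common reactions, and section 7 says that flu-like effects occur regularly. All fall under Table 6. About 20 sites will apply it.

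In Table 3, a reduced-dose step that follows a hold should end on a condition that separates patients who are ready for the standard dose from those who are not. The stated thresholds do not do that at the moment of restart. At stake is whether arm A dosing after a grade II event, or after severe cytopenia, follows one rule or each investigator's reading.

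**Working it through.** The document gives no figure for this point. The check sets the rows side by side and compares thresholds.

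**Step 1: Table 6, instruction by grade**

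| Grade | Row I - II | Row II | Row III | Row IV |
|---|---|---|---|---|
| I | no change | – | – | – |
| II | no change | 50 µg every 2 weeks | – | – |
| III | – | – | pause until grade I or II | – |
| IV | – | – | – | stop |

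Grade II is the only grade with two entries. No qualifier, such as first or repeated event, duration or tolerability, separates them.

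**Step 2: size of the difference at grade II**

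- Patient on 100 µg: 100 µg under the first row, 50 µg under the second. Ratio 100 / 50 = 2.
- Patient on 50 µg, in the lead-in or after a reduction: 50 µg under either row. Ratio 50 / 50 = 1.
- Patients who could be exposed: at most the arm A allocation, 214 / 2 = 107. The number who will have a grade II event on 100 µg is not given and cannot be derived.

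**Step 3: Table 3, restart against re-escalation**

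| Trigger | Restart at 50 µg when | Return to standard dose when | Met at restart? |
|---|---|---|---|
| ANC < 500 | ANC ≥ 1000 | ANC > 750 | always, since 1000 > 750 |
| Platelets < 25,000 | ≥ 75,000 | > 75,000 | always, except at exactly 75,000 |

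The other two rows involve no hold. For ANC below 750, reduction and return use the same value, so the problem does not arise. For platelets below 50,000, the row has no return value and only the general sentence above the table applies.

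**Step 4: does this reach the primary analysis?** Section 16.7 analyses efficacy in all randomized patients by allocated arm, whatever treatment they went on to receive. The sample size in section 16.10 rests on relapse-free survival of 45% against 65% and a 10% drop-out: 192 / 0.9 = 213.3, rounded up to 214. Neither uses the dose tables.

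**The case against.** **The tables are only recommendations.** Their titles say so, although section 10.3.1.1 states that modifications will be performed. Discretion does not resolve Table 6, because the table recommends both changing and not changing the dose.

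**The duplicate row may come from the PDF conversion.** The four rows are intact and in order. Reading the second row as grade III would only move the duplication to grade III.

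**Table 3 can be followed in sequence.** This objection largely stands. Both rows call for monitoring after restart, so the increase can be tied to a later count. Even then, the ANC criterion withholds the increase only if the count falls from 1000 or more to 750 or less, and the row does not say which count decides. This is a redundant threshold and not a pair of opposite instructions, so it ranks below Table 6.

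**Stronger readings that the document does not support:**
- A reader might infer that dosing will differ by site. The protocol shows only that it can differ between investigators and sites.
- A reader might infer that the per-protocol set is compromised. Section 16.2 excludes only major deviations and names no dosing rule. Nothing shows that following either row would count as one, and the per-protocol analysis is a sensitivity analysis.
- A reader might infer that there is no way back after platelets below 50,000. The general sentence above Table 3 covers that case, though it is discretionary and has no threshold.
- A reader might infer a demonstrated safety hazard. The document shows no harm from either reading, and it does not show which is right.

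**Conclusion.** The contradiction in Table 6 is established on the face of the protocol and has to be corrected: an operative dosing rule gives two answers for grade II. The consequence is a possible two-fold dose difference, limited to patients on 100 µg when the event occurs. Its frequency cannot be estimated from the document.

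The Table 3 point is confirmed by arithmetic but is secondary. After ANC below 500 and platelets below 25,000, the restart count already satisfies the re-escalation threshold, apart from the single platelet value of 75,000.

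These conclusions rest on a literal reading of the tables and on there being no qualifier elsewhere in the protocol. The ITT comparison and the planned 214 patients stand as they are.

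**What to change.** - **Table 6:** the sponsor must reconcile the two grade II rows so that each grade carries one instruction, and check that the grade III row then leads to a single answer for a patient who recovers to grade II.
- **Table 3:** the sponsor must reconcile the restart and re-escalation thresholds after ANC below 500 and platelets below 25,000, so that each step has its own condition. It should also make clear whether the general sentence is meant to be the only guidance after platelets below 50,000.

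Which instruction or threshold applies is for the sponsor's medical team; none is proposed here. The cost is a protocol amendment to two tables and a notice to sites. No change to the sample size or the confirmatory analysis is needed.

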## 10.4 Manufacturer of Study Medication

In brief, the drug substance production is performed as a four-stage process at 40 L scale:

- (1) Fermentation and E. coli cell harvest,
- (2) Isolation of P1040 drug intermediate (Proline-IFN $\alpha$ -2b) inclusion bodies,
- (3) Refolding and purification of P1040 drug intermediate, and
- (4) Pegylation, purification, and formulation of final Ropeginterferon alfa-2b drug substance (AOP2014)

The study medication will be manufactured by AOP Orphan Pharmaceuticals AG (Austria).

## 10.5 Handling and Storage of the Medication

Before injection, pen containing the AOP2014 should be kept at room temperature for 10 min. After cleaning the injection site with an alcohol swab, the correct dose of AOP2014 will be self-administered by the patient according to the instructions given by the treating study physician and the Instructions for Use provided with the pen. Self-administration will be documented in the e-CRF. A patient diary will be provided and shall help the patient to document AOP2014 injections, injected dose of AOP2014, side effects, and concomitant medication, if necessary. Since a pre-filled auto-injection pen contains 0.5ml of AOP2014, equivalent to 250  $\mu$ g active substance, each pen can be used for two injections using disposable needles that must be fixed to the pen before the infection. Thus, each pen contains sufficient substance for up to 4 weeks.

AOP2014 study medication must be stored until use in the fridge (2-8°C), in the outer carton in order to protect from light.

At the study center the refrigerator will be located in a locked room accessible only to authorized personnel. The temperature will be recorded on a temperature log.

Patients will be instructed to transport and store study medication at home, according to the storage requirements.

## 10.6 Reference Document

The current version of the AOP2014 Investigator's Brochure (IB) is kept in the Investigator Site File (ISF). The AOP Orphan Pharmaceuticals AG is responsible for updates of the reference document and KKS Marburg for passing on the Coordinating Investigator, Ethics Committee, and Competent Authority and to the study centers. In case of changes in the IB the Coordinating Investigator has to re-evaluate the risk-benefit assessment of the study.

## 10.7 Labeling, Drug Supply and Accounting

CSM Clinical Supplies Management Europe GmbH will provide sites with the study medication at the request of KKS Marburg.

Study medication will be delivered to the study centers in the cooled containers. 1 pre-filled auto-injection pen with 0.5ml active AOP2014 substance and 2 injection needles will be packed together in the paper carton box. Pens and cartoon packages labels will comply with the legal requirements of Germany and will be printed in German. They will supply no information about the patient.

At the study center, the responsible designated site personnel have to confirm the receipt of study drug, by completing and faxing the enclosed form to CSM Clinical Supplies Management Europe GmbH (contact details on the form). The confirmation of receipt (in original) has to be filed in the ISF. The investigator must maintain an accurate record of the shipment in a drug accountability form. At the study center the study medication must be handled and stored safely and properly, and kept in a secured location to which only the investigator and designated site personnel have an access. Upon receipt it has to be stored according to the instructions specified on the labels.

Study medication will be dispensed at the investigator's site by an authorized person. On each label designated site personnel has to fill in the adequate Pat.ID (first 2-digits will be a site number and next 3-digits will refer to sequencing number of the patient). Each patient will be provided with an instruction for use and an adequate supply for self-administration at home until their next scheduled visit. All study treatment dispensed will be recorded in a patient specific drug accounting log. Moreover, patients have to return all carton boxes and pens either containing unused study drug or the empty one, on a regular basis, at the end of the study, or at the time of study drug discontinuation. The Investigator or his/her designee will account for all study medication dispensed and returned.

At the conclusion of the study and, as appropriate during the course of the study, the Investigator will return all unused study pens, drug labels and a copy of the completed drug accountability forms. Unless specifically instructed by KKS Marburg, beside from used pens the Investigator must not destroy any carton boxes, drug labels, or unused drug supply. Only after receiving written authorization by KKS Marburg, the Investigator will be instructed to either send all of the pens (containing unused study drugs) to the address provided at the time of authorization for destruction or to dispose of unused drug according to local regulations. Each disposal has to be documented and filed in the ISF.

All drug supplies are to be used only for this protocol and not for any other purpose.

### **10.8 Prior and Concomitant Therapy**

Medication for concomitant diseases should be continued and will be documented in the e-CRF. Any experimental therapy is not allowed while on study. In addition, the TKI or immune-stimulatory (e.g. IFN) or immune-suppressive medication (e.g., steroids) are contra-indicated during the course of the study. However, musculoskeletal pain may occur in up to 30% of the patients within 1-6 weeks after TKI discontinuation. Symptoms then resemble rheumatic polymyalgia. They should be treated with paracetamol or non-steroidal anti-inflammatory drugs. Since corticosteroids may offset the effects of AOP2014, steroids should generally not be prescribed. Only in the rare cases that intolerable symptoms occur, steroids may be given at 10-20 mg prednisone p.o. and tapering within 2 weeks. Patients cannot be vaccinated 1 month prior or during the period of study medication application.

## **11 Study medication (non-IMP)**

### **11.1 Characteristics of non-Investigational Medicinal Product (non-IMP)**

TKI is administered in the same way as before the start of the study for one more month. Trade is used for this purpose.

### **11.2 Side effects caused by discontinuation of TKI therapy:**

In approximately 20% of the patients, a "discontinuation syndrome" may occur after discontinuation of the TKI tablets. This means that the following symptoms may occur:

Bones and muscle pain, joint and tendon pain, joint inflammation (preferably the upper extremities of the shoulder girdle and the cervical spine)

The symptoms begin approximately 21 days after discontinuation of therapy and last up to months.

More frequently affected are patients who had already had bone joint and muscle problems earlier, or a particularly long TKI therapy.

In addition, a deterioration of an existing diabetes mellitus was observed and the occurrence of acne.

## 12 Study Procedures and Methods

### 12.1 Study Procedures

#### 12.1.1 Screening Visit and Registration

CML patients having been treated with TKI for at least three years and being in at least MR^4 or better MR will be informed by the investigator about the purpose, risks and benefits of the ENDURE-CML study. Patients will obtain adequate time to consider participation in the study. The informed consent has to be signed at the clinic, during the Screening Visit at the latest and prior to any study-related assessment or procedure (see Table 1 and Table 2).

Eligible female patients with childbearing potential will continue to use highly effective methods of contraception as advised and standard for TKI treatment.

#### The Screening Visit includes:

- Obtain signed written informed consent before performing any study-related procedures
- Verification of inclusion and exclusion criteria
- Relevant demographics, Sokal, EUTOS, EURO and ELTS score
- Recording of medical and pre-treatment history
- Physical examination, vital signs and body temperature
- ECOG performance score
- BCR-ABL-PCR test at study reference laboratory in Jena or Mannheim
- Clinical Laboratory Evaluation
- Serum pregnancy test
- Serum HIV test
- Serum test for excluding active and chronic hepatitis B and C
- Autoimmunity (ANA, TSH) screen
- Assessment of concomitant medications and AEs

 If the patient will not meet all the inclusion criteria / fulfill the exclusion criteria, or will withdraw his informed consent before the randomization, he/she must be registered by KKS Marburg using the Screening/Randomization form (filled in the ISF).

